# The ICU-Diary study: prospective, multicenter comparative study of the impact of an ICU diary on the wellbeing of patients and families in French ICUs

**DOI:** 10.1186/s13063-017-2283-y

**Published:** 2017-11-15

**Keywords:** ICU diary, Intensive care unit, Stress disorders, post-traumatic, Family, Anxiety, Depression

## Abstract

**Background:**

Post-intensive care syndrome includes the multiple consequences of an intensive care unit (ICU) stay for patients and families. It has become a new challenge for intensivists. Prevention programs have been disappointing, except for ICU diaries, which report the patient’s story in the ICU. However, the effectiveness of ICU diaries for patients and families is still controversial, as the interpretation of the results of previous studies was open to criticism hampering an expanded use of the diary. The primary objective of the study is to evaluate the post-traumatic stress syndrome in patients. The secondary objectives are to evaluate the post-traumatic stress syndrome in families, anxiety and depression symptoms in patients and families, and the recollected memories of patients. Endpoints will be evaluated 3 months after ICU discharge or death.

**Methods:**

A prospective, multicenter, randomized, assessor-blind comparative study of the effect of an ICU diary on patients and families. We will compare two groups: one group with an ICU diary written by staff and family and given to the patient at ICU discharge or to the family in case of death, and a control group without any ICU diary. Each of the 35 participating centers will include 20 patients having at least one family member who will likely visit the patient during their ICU stay. Patients must be ventilated within 48 h after ICU admission and not have any previous chronic neurologic or acute condition responsible for cognitive impairments that would hamper their participation in a phone interview. Three months after ICU discharge or death of the patient, a psychologist will contact the patient and family by phone. Post-traumatic stress syndrome will be evaluated using the Impact of Events Scale-Revised questionnaire, anxiety and depression symptoms using the Hospital Anxiety and Depression Scale questionnaire, both in patients and families, and memory recollection using the ICU Memory Tool Questionnaire in patients. The content of a randomized sample of diaries of each center will be analyzed using a grid. An interview of the patients in the intervention arm will be conducted 6 months after ICU discharge to analyze in depth how they use the diary.

**Discussion:**

This study will provide new insights on the impact of ICU diaries on post-traumatic stress disorders in patients and families after an ICU stay.

**Trial registration:**

ClinicalTrial.gov, ID: NCT02519725. Registered on 13 July 2015.

**Electronic supplementary material:**

The online version of this article (doi:10.1186/s13063-017-2283-y) contains supplementary material, which is available to authorized users.

## Background

Hospitalization in an intensive care unit (ICU) is a stressful experience for both patients and families, as they are facing an unknown environment, diagnostic and prognostic uncertainty, and possible fears of dying and of having an impaired quality of life. The progression of intensive care therapies is associated with decrease of in-ICU and in-hospital mortality [1–4]. However, this reduction in mortality is not the main criteria for the patients’ and families’ evaluation of their ICU stay, as the wishes of most survivors are to regain their personal and professional lives [5–7].

For several years, attention has been focused on the ICU being the origin of patients’ and family’s sequelae [8–10]. In 2012, a conference of stakeholders representing key organizations and groups of North America described the “post-intensive care syndrome” (PICS) as including physical, cognitive and psychological consequences of ICU stay for patients (PICS) and families (PICS-F) [11, 12]. Although there is a lack of basic scientific evidence enabling the understanding of the pathological mechanisms of post-ICU morbidity, experts agree on the importance of ICU events (hypoxia, shock, inflammation, glucose dysregulation), ICU treatments (use of benzodiazepines and other sedatives), and ICU conditions (bed immobilization, physical restraint, discomforts like noise, pain, thirst) [13]. Cognitive impairments can persist in 30 to 80% of patients. More than 6 months after hospital discharge, anxiety, depression, and post-traumatic stress-related syndrome (PTSD) are described in 8–57%, 23–48%, and 10–50% of patients, respectively [14]. Herridge et al. described four post-ICU disability stages based on age, duration of ICU stay and physical functional dependency 1 week after ICU admission, without significant differences in cognitive status [15]. At 6 months, anxiety, depression symptoms, and PTSD were described in 15–24%, 5–36%, and 35–57% of the families, respectively [16]. To cope with these syndromes, 8 to 32% of families used medications after ICU admission; the ICU stay interfered with their lifestyle in half of them while they were caring of their relatives [16]. Most of ICU survivors required relative’s assistance after their ICU stay, adding additional burden to their own life, especially depressive symptoms for up to 1 year [17]. These findings suggest that critical illness affects long-term outcome not only in patients but also in their relatives, increasing the effect of critical illness and societal burden. Some experts spoke about the “hidden public health disaster” [18]. Prevention programs are needed to limit these consequences.

Several prevention programs have focused on psychological consequences, and results were often disappointing [19–26]. Three types of prevention programs were evaluated: early in-ICU psychological interventions, post-ICU coping skill interventions through phone visits for outpatients, and ICU diaries. In a single, before-after study, the intervention of a psychologist for trauma patients providing stress support and coping strategies for management of anxiety, depression, PTSD, fear, and discomfort yielded a significant decrease in the PTSD syndrome [26]. Jones et al. included ventilated patients in a randomized controlled trial with blinded follow-up that evaluated an intervention associating a manual with recommendations of physical exercises, psychosocial and psychological advices, and thrice weekly phone calls reinforcing the use of the manual. This intervention showed conflicting results, with no effect on anxiety, depression or PTSD, and a significant increase of quality of life up to 6 months [19]. In a single, small, randomized controlled study of 21 survivors, Jackson et al. showed that a cognitive, physical, and functional rehabilitation had an effect in improving cognitive performance [24]. As the studies are scarce and limited, the level of evidence for promoting these interventions is currently weak.

One of the explanations for the emotional troubles experienced by these patients is the lack of memories or the presence of delusional memories of their ICU stay [27, 28]. The intervention tested to fill the memory gap has been the ICU diary [29]. The ICU diary has been used for 30 years in North Europe and further extended to other European countries, North America, and Australia [30–32]. The diary is prospectively written in an everyday language and builds the patient’s story. It contains the reason of admission, a daily narrative of activity, and a conclusion before transferring the patient to the ward, or condolence for the family for the decedents. Every entry is signed and the diary may contain different numbers of entries. Entries are mainly made by the bedside nurse; families are encouraged to write in it; in some countries, physicians also participate to construct the patient’s story [22, 31, 33, 34]. Several studies explored the influence of the diary on the psychological consequences of the ICU stay on patients and families. A European randomized study included 372 patients with an ICU stay of more than 72 h, where half of them received the diary 1 month after ICU discharge. The onset of PTSD was reduced from 13 to 5% in the group of patients having received the diary [35]. A French single-center study including patients with an ICU stay of more than 96 h showed that the ICU diary was associated with a decrease of PTSD syndrome in patients and families 1 year after ICU discharge [22]. Some recent reports reviewed the impact of diaries on patient’s recovery and yielded conflicting results due to methodological features [36–38]. Studies of impact were single-center studies [20, 22], with different patient case-mix [22, 39], and those where diaries were written by different categories of caregivers. The evaluation of the impact, and the methodology used (qualitative or quantitative) differed between studies [21, 40, 41]. These differences did not recommend the use of a diary in routine clinical practice.

These findings prompted us to design the ICU-Diary study to overcome these limitations and clarify the impact of an ICU diary on patients and families.

## Methods

### Study design

The ICU-Diary study is a multicenter, randomized, parallel (allocation ratio 1:1), and controlled study to assess the impact of the ICU diary on the wellbeing of both patients and families. We designed a quantitative study to assess the psychological effect of the diary and a qualitative study to examine how the patient used his diary 6 months after ICU discharge. The study was not blinded for the ICU staff but assessment was blinded for the psychologist processing the follow-up. The study timeline and schedule of enrollment, interventions, and assessments is presented in Fig. 1. The Standard Protocol Items: Recommendations for Interventional Trials (SPIRIT) Checklist is provided in Additional file 1.

**Fig. 1 Fig1:**
[figure not shown]
Study timeline, schedule of enrollment, interventions, and assessments

### Aims

The primary objective is to evaluate the PTSD in patients 3 months after ICU discharge as measured by the Impact Event Scale-Revised questionnaire (IES-R). The IES-R is a validated and reliable tool for the evaluation of PTSD symptoms of intrusion, avoidance, and hyperarousal [42]. Each item is scored on a 5-point Likert-type scale (0, not at all; 1, rarely; 2, occasionally, 3, fairly often; and 4, often). The total score can range from 0 (no symptoms) to 88 (severe symptoms). The main criteria of measurement will be the score of PTSD as having a a low or high IES-R score, using 22 as the cutoff, as previously used in ICU studies [43].

The secondary objectives are to evaluate:The PTSD in families 3 months after ICU discharge, using the IES-R scale [42]. The criteria of measurement will be the score of PTSD as having a low or high IES-R score, using 22 as the cutoff, as previously used in ICU studies [43]Anxiety and depression symptoms in patients 3 months after ICU dischargeAnxiety and depression symptoms families 3 months after ICU discharge. Symptoms of anxiety and depression are assessed using the validated French version of the self-administered Hospital Anxiety and Depression Scale (HADS), which has seven items on anxiety and seven on depression [44]. The sum for each domain ranges from 0 to 21. A score at 7 or below is considered normal. The cutoff score of 8 for each of the two subscales defines severe symptoms of anxiety or depression [45]The recollection of memories of the ICU stay by the patient 3 months after ICU discharge, as measured by the ICU Memory Tool Questionnaire [46]. The ICU Memory Tool Questionnaire consists of items exploring recollections of the patient before and during their ICU stay. It also includes two questions to assess if PTSD symptoms are present. As no French version exists, the ICU memory tool questionnaire was translated and back-translated into French by bilingual researchers, namely a French native who speaks English and an English native who speaks FrenchDiary content analysisThe content of a random sample of the study diaries will be analyzed with a grid (Table 1) that has already been published [22]. This grid was built with a panel comprising 11 members (three ICU physicians including two from other units, one ICU nurse, two psychologists, two hospital visiting volunteers, one person from the general population with a history of admission to another ICU, one former patient of our ICU, and his wife) using a Delphi technique. Six categories were defined and will serve for the analysis of the content of the diaries. We will report quantitatively the categories and themes which are represented most often in the diaries and will give verbatim examples for each of them.

**Table 1 Tab1:** Grid of analysis of the content of the intensive care unit (ICU) diary

Category 1: Defining places, spaces, and people	
Theme 1	Narrative about the ICU and its location in the hospital and city
Theme 2	Narrative about the identity and job responsibilities of each ICU staff member
Theme 3	Narrative about the characteristics of the room
Theme 4	Narrative describing the pictures posted in the room
Theme 5	Narrative about the characteristics and purpose of the machines
Theme 6	Narrative about the sights and sounds in the room
Theme 7	Narrative about the presence of, or visits by, members of the clergy
Category 2: Building a time flow of medical events	
Theme 1	Narrative about the patient’s history before ICU admission and after the first urgent interventions
Theme 2	Narrative about the condition of the patient, clinical course, treatments, procedures, investigations, and surgeries
Theme 3	Description of events that interfered or might have interfered with the presence of ICU staff members at the bedside
Theme 4	Comments on life expectancy and the expected impact of the disorders on quality of life
Theme 5	Narrative describing exchanges among healthcare professionals involved with the patient: date of onset and content
Theme 6	Narrative about the differences in tasks carried out by the day staff and night staff, to explain how the 24-h cycle unfolds
Category 3: To replace the time flow of the patient’s experience within the time flow of family, community, and world events	
Theme 1	Narrative about events in the patient’s personal life (narrator, family, friends …)
Theme 2	Narrative about the difference in the perceived time flow of events between the patient since ICU admission and the narrator or family/friends
Theme 3	Narrative about future projects for the patient
Theme 4	Narrative about concomitant social, political, economic, and cultural events
Theme 5	Narrative about the visits, their sequence in time, their duration, and factors that prevented some visits from occurring
Category 4: To demonstrate the continuity of the patient’s life	
Theme 1	Narrative about the patient’s recent or remote past, habits, reactions, and personality features
Theme 2	Narrative about the patient’s behaviors, attitudes, and actions
Theme 3	Narrative about physical changes and attitudes (e.g., ability to open/close the eyes)
Theme 4	Narrative about changes in expressions of pain and responses to nursing care
Theme 5	Narrative about the patient’s emotional responses to the voices of the staff and family/friends (smiling, small movements of the eyelids or body)
Theme 6	Narrative about the patient’s emotional responses to physical contact (stroking, holding hands, touching …)
Category 5: To express feelings and emotions	
Theme 1	Narrative that explicitly describes feelings or emotions about the patient
Theme 2	Narrative that explicitly describes feelings or emotions about or toward the ICU staff
Theme 3	Narrative that explicitly describes feelings or emotions of family members or other loved ones
Theme 4	Narrative describing expectations, fears, discouragement, and hopes of the family and other loved ones
Theme 5	Narrative describing the fears and hopes of the staff
Category 6: To explicitly demonstrate the presence, commitment, and support of staff and family	
Theme 1	To write an account of one’s presence at the patient’s bedside
Theme 2	To make one’s presence felt in a personal and original way (poems, songs, music, drawings …)
Theme 3	To describe relationships between the patient and other persons while encouraging the other persons to speak to, and to touch, the patient, despite the unfavorable environment
Theme 4	To describe one’s physical involvement in communicating with the patient
Theme 5	To describe or refer to one’s support in the form of prayers or any other religious or spiritual activityThe way the patient uses the diary will be explored through a qualitative approach, analyzing semidirective interviews with the patients of the intervention arm, performed 6 months after the ICU discharge using thematic and interpretative phenomenological analysis.

Primary and secondary objectives are measured by a psychologist hired for the study. The psychologist will be blind to the randomization arm when they will phone patients and families. If patients or a family member speak about the diary during the interview, the number of unblinded interviews will be reported in the study flow chart.

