### Intervention

The intervention is the elaboration of an ICU diary by caregivers and families. All the diaries for every center are built on the same way by the main investigator and given to the different centers before the beginning of the study. The first page is standardized and includes an explanation of the purpose of the diary; then the diary includes a picture of a typical patient’s room with an explanation of the different devices possibly used during the stay, pictures of the unit, and a list of the main responsible persons of the unit. The diary is maintained by the family and by the ICU staff. The only instruction given to the families and staff members about diary entries is to refrain from writing about confidential matters that could not be shared among the patient, all relatives, and the staff. Staff members are free to express compassion and their hope, or absence thereof, that the patient would recover. Relatives can speak freely with the patients without guidance from the ICU staff. The first entry is written immediately after randomization by the ICU physician and includes a summary of the reason for admission, the name of the ICU and of the hospital, and a summary of the events of the first 48 h. Then, each day, a brief entry is mandatory during the whole ICU stay. This entry can be done by an ICU staff member whatever their category. Relatives are not encouraged to take photos of the patient during the whole stay without the patient’s permission. No patient’s photos taken during the ICU stay are allowed in the ICU diary, only pictures taken prior to the ICU stay (which were taken with the patient’s authorization). For patients in the intervention arm, they received the ICU diary at the conclusion of their ICU stay when they are discharged to wards. If the patient dies, the diary is given to the family if they are present in the unit or sent by mail with an identical letter for all ICUs. A guide for the elaboration of the ICU diary was given to each center containing: rules for writing in the diary, indications for opening and maintaining the diary, for writing that the patient status does not fit well when the clinical patient status impaired, and for relinquishing the diary at ICU discharge. Examples of verbatim narratives of different categories of healthcare workers (ICU physician, resident, nurse, nursing assistant, physiotherapist) are included in the guide. World Health Organization Trial registration Data Set is provided in Additional file 3.

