### Arms

#### Intervention arm

An ICU diary is opened by the ICU staff for the patient and their relatives at 48 h after ICU admission. It will be given to the patient at ICU discharge or to his family in case of death.

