## Discussion

With the development of the technical ICU, the prevention of sequelae is an increasingly important health problem. Reducing the psychological consequences of the post-intensive syndrome is one of the major challenges for intensivists. This study should provide insights on the impact of the ICU diary on post-traumatic consequences for patients and for their families. This tool has no financial cost, except the time offered by the caregivers to patients and family for filling it in. Until now, the ICU diary has been used in some ICUs, particularly those focused on patient- and family centered care. If a positive effect of the diary is demonstrated, it could be included in programs of patient- and family centered care in France and in countries where ICU organization and healthcare worker to patient ratio is similar to that in France.

However, some issues related to this study design should be discussed. First, the fact that the intervention is not blinded for the healthcare workers should be considered in the results. Healthcare workers might provide more support to patients and families in the diary group because their relationship could be modified by the fact of giving more time and more attention to the patient and their family through the diary filling. However, the limitation of 10 diaries by center should limit this phenomenon, as each center should rarely have more than one patient at once with a diary. Although the results of the study will not enable us to differentiate what is important in a diary: the tool, the narrative or the relationship with the healthcare team. Nevertheless, we chose to perform a content analysis by two psychologists using a previously published grid. This will permit a qualitative description of the diaries content, which will contribute to explaining the results.

The fact that patients or families may mention their diary during the interview and reveal their randomization arm is another study limitation. However, such cases will be noticed in the flow chart of the study. In addition, this bias is limited by the fact that the interview will use questionnaires focusing only on anxiety, depression, and post-traumatic symptoms. The questionnaire about the memory recollection has not open questions but only questions with some suggested answers. So it is close question compared to open questions when the patient can freely speak.

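### The 3-month memory comparison cannot separate what the patient recalls from what the patient has read in the diary, so it should not be reported as a result on recollection

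*Protocol article*

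**What the plan says.** Among the secondary objectives in the Protocol article (Aims) is the "recollection of memories of the ICU stay by the patient 3 months after ICU discharge", measured with the ICU Memory Tool. The abstract gives the same time for the endpoints generally: "Endpoints will be evaluated 3 months after ICU discharge or death". No earlier memory assessment is mentioned in the text; the schedule in Fig. 1 is not shown.

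On handover, the Intervention section says of diary-arm patients that "they received the ICU diary at the conclusion of their ICU stay when they are discharged to wards", and the Intervention arm section agrees: "It will be given to the patient at ICU discharge or to his family in case of death". Under Control arm, no diary is opened.

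On content, the Intervention section requires a first entry giving the reason for admission and the events of the first 48 h, then an entry every day. The diary also holds a picture of a typical room "with an explanation of the different devices possibly used during the stay".

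On question format, the Discussion states: "The questionnaire about the memory recollection has not open questions but only questions with some suggested answers". It offers this as a protection of assessor blinding.

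**The concern.** The objective names recollection, which is what the patient remembers. The intervention is a written account of the same stay, handed over about 3 months before the patient is asked. With closed prompts a patient need only recognise a suggested answer, and having read about an event or a device may be enough for that. Randomization does not remove the problem, because the reading comes after it and is part of the treatment.

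What is at stake is the meaning of the result. The Background treats missing and delusional memories as one explanation of later distress and says: "The intervention tested to fill the memory gap has been the ICU diary". Against that text, more reported memories in the diary arm would readily be taken as restored recollection and as support for the mechanism, although reading alone could produce the same answers.

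**Working it through.** **Order of events and overlap of content (Protocol article)**

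| Element | Diary arm | Control arm | Section |
|---|---|---|---|
| Written account of the stay | Held from ICU discharge | None | Intervention arm; Control arm |
| Family able to visit, so able to tell the patient about the stay | Yes | Yes | Recruitment of patients |
| Memory questionnaire | 3 months, closed | 3 months, closed | Aims; Discussion |
| Diary use explored | 6 months, qualitative | Not applicable | Aims; Qualitative analysis of patient interviews |

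The tool is described as covering the time before and during the ICU stay. The content grid in Table 1 includes history before admission, treatments and procedures, machines, and sights and sounds in the room. The diary can therefore cover the period that the tool asks about. The only enquiry into diary use comes after the memory interview, and no link to the memory answers is described.

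**The plan's own figure.** The only stated design figure is the sample size, which concerns the primary endpoint. With 40% against 26%, two-sided 0.05, power 80% and mean proportion 0.33:

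n = [1.96 × √(2 × 0.33 × 0.67) + 0.8416 × √(0.40 × 0.60 + 0.26 × 0.74)]² / 0.14² = 175.9, so 176 per arm and 352 in all, as stated.

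The concern does not depend on this figure; 176 is used below only as a scale.

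**Illustration; every input is assumed.** Let p be the share who truly recall an item, equal in both arms. Let d and k be the shares of non-recallers in the diary and control arms who endorse it from second-hand knowledge. Then

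false difference = [p + (1 − p)d] − [p + (1 − p)k] = (1 − p)(d − k).

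Take p = 0.50 and d = (share who have read the diary) × (share of non-recalling readers who endorse the item), from 0.6 × 0.2 = 0.12 to 0.8 × 0.4 = 0.32.

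- If k = 0: 0.5 × 0.12 = 6 points to 0.5 × 0.32 = 16 points.
- If k = 0.12, because families inform control patients too: 0.5 × (0.12 − 0.12) = 0 points to 0.5 × (0.32 − 0.12) = 10 points.

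**Chance of a significant difference on one yes/no item** with 176 per arm, two-sided 0.05 and no true effect on recollection. The rows give control-arm endorsement p. The columns give the share c of the remaining diary patients who endorse the item only because they read it, so the diary-arm rate is p + (1 − p)c.

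| p | c = 10% | c = 20% | c = 30% |
|---|---|---|---|
| 30% | 0.28 | 0.78 | 0.98 |
| 50% | 0.15 | 0.47 | 0.82 |
| 70% | 0.09 | 0.24 | 0.49 |

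Depending on inputs that the documents do not give, reading could matter little or could nearly guarantee a significant difference. The scoring of the tool is not shown, so a single item stands in for it.

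**The case against.** The strongest reply is that filling the memory gap is the purpose of the diary, so a randomized difference in reported memories is a real effect of the intervention and not an error. That stands for the effect on answers. It does not stand for the word recollection, which is how the objective is put.

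Second, the protocol never says that more memories would count as benefit, and memory is not among the five latent variables of the example path model. Both are true. The risk lies in how the result would be read beside the Background, not in a stated plan to misread it.

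Third, the tool's item list is not shown, and scoring may properly be left to an analysis plan. This limits how precisely one can say which items are affected. An analysis plan can restrict interpretation, but it cannot recover a distinction that was not collected.

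A reader might infer three stronger things that the documents do not support:

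- That the error falls on the diary arm alone. Every enrolled patient must have a family member able to visit, so second-hand knowledge exists in both arms.
- That a higher memory count in the diary arm is all but built in. No figure says how many patients read the diary, or how many endorse what they only read.
- That delusional memories would be a clean substitute comparison. A patient who reads a factual account may stop endorsing something that did not happen, which is also an effect of reading.

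**Conclusion.** The point holds as a limit on interpretation. The diary comes before the only memory assessment described, the questions are closed, and nothing described separates recalled from read. The difference between arms is valid as an effect on reported memories, but it cannot be concluded to be an effect on recollection.

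The size of any bias cannot be derived from the documents. The range of 0 to 16 percentage points is an illustration on assumed inputs, not an estimate. The conclusion also assumes that Fig. 1 shows no memory assessment before the diary is handed over.

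One secondary endpoint is affected. The primary endpoint and the randomization are not. It is a minor point.

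**What to change.** Restate the secondary objective and its between-arm result as reported memories or knowledge of the stay, whether recalled or read. State that no conclusion on improved recollection, or on the memory-gap mechanism in the Background, will be drawn from it.

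If the tool's items allow, report delusional memories separately from items that the diary can supply. Add that reading the diary may change those answers too, so they are not a bias-free replacement.

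This needs no new data and no further calls. The cost is that the memory comparison loses its status as evidence of recollection.
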